### 2.12 Data Monitoring

Given the minimal risk associated with the study, the Institutional Review Board 
of the Second Affiliated Hospital of Xinxiang Medical University waived the 
requirement for a data monitoring committee.

### 2.13 Harms

To examine the safety of HD-tDCS and track any adverse reactions participants 
might experience, an adverse reaction scale will be employed. An adverse reaction 
assessment form specific to HD-tDCS was developed for this study, encompassing 
common adverse reactions such as headache, skin tingling, fatigue, itching, 
burning sensations, and local discomfort. The design of this scale facilitates 
the prompt identification and management of any issues that may arise during the 
process. In the event of a serious adverse reaction, the current therapy will be 
discontinued, appropriate health evaluations will be conducted, and the incident 
will be communicated to the ethics committee. All adverse events will be 
systematically recorded in the CRF with respect to their incidence, types, and 
severity. The final study results will include a comprehensive summary of adverse 
events for each study group (Groups 1–4), including the frequency, severity, and 
percentage of participants affected by each type of adverse event. This will 
enable safety comparisons across the different interventions. To mitigate 
potential adverse reactions associated with the study, professional therapists 
will be engaged to implement the therapy, and they will receive comprehensive 
training pertinent to the study.

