## 2. Methods

### 2.1 Study Design 

This study is a prospective, double-blind, randomized controlled trial protocol 
to assess the efficacy of HD-tDCS combined with CCRT in enhancing cognitive 
function among patients with schizophrenia. Eligible participants will be 
recruited and randomly allocated into four groups using a random number table: 
the HD-tDCS + CCRT group (Group 1), the HD-tDCS group (Group 2), the CCRT group 
(Group 3), and the control group (Group 4). Assessments will be carried out at 
baseline (T0), after 10 sessions (T1), after 20 sessions (T2), and after six 
months of follow-up (T3). Research framework is illustrated in Fig. 1. 
Participants in the control group (Group 4) will continue to receive their stable 
regimen of antipsychotic medication and standard clinical care, without 
undergoing any HD-tDCS or CCRT sessions.

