### 2.6 MRI-guided High-Definition Transcranial Direct Current 
Stimulation

MRI scans will be employed to construct detailed anatomically realistic head 
models. The development and simulation of head models for the HD-tDCS-induced 
electric field use the SimNIBS software (version 4.5, SimNIBS Group, Copenhagen, 
Denmark) [30]. Eight distinct 4*1 montages centered on the mPFC will be used to 
simulate the E-field for each brain. The normal component of the E-field will be 
calculated using the finite element method [31]. Based on T1 and T2 MRI scans, 
head models will be constructed from these images, incorporating five different 
tissues: skin, skull, white matter, gray matter, and CSF. Finally, the mPFC will 
be identified in each subject’s brain according to the Ranta atlas [32]. The 
study will utilize an MRI-guided HD-tDCS device (model MxN-9-9002A, Soterix 
Medical, New York, NY, USA). The central electrode will be positioned over the 
mPFC. The four surrounding cathodes will be positioned at frontal sites Fp1, Fp2, 
F7, and F8. The current intensity will be maintained at 2 mA. Each HD-tDCS 
session will involve the delivery of a 2 mA direct current for a duration of 30 
minutes. HD-tDCS will be conducted 5 times per week, over a 4-week period, 20 
sessions. During the therapy period, patients will continue their existing 
pharmacological treatment regimens without any modifications.

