### 2.9 Outcome

The primary outcome measure used in this research is the MATRICS Consensus 
Cognitive Battery (MCCB), which is a crucial tool for assessing cognitive 
deficits in schizophrenia. It evaluates seven distinct cognitive domains: working 
memory, abstract thinking, attention/vigilance, processing speed, visual 
learning, verbal/visual learning, reasoning and problem-solving. The battery 
comprises the following subtests: (1) Trail Making Test A (TMT-A), (2) Symbol 
Coding, (3) Hopkins Verbal Learning Test-Revised (HVLT-R), (4) Digit Span Test 
(DST), (5) Stroop Color-Word Test, (6) Spatial Span Test (derived from the 
Wechsler Memory Scale III, WMS-III), (7) Verbal Fluency Test (VFT), (8) Mazes, 
(9) Brief Visuospatial Memory Test-Revised (BVMT-R), and (10) Continuous 
Performance Test-Identical Pairs (CPT-IP).

Secondary outcome measures include the Brief Psychiatric Rating Scale (BPRS), 
the PANSS, the Clinical Global Impression 
(CGI) scale, the Social Disability Screening Schedule (SDSS), the Schizophrenia 
Quality of Life Scale (SQLS), and fMRI. Specifically, the general information 
questionnaire is utilized to collect basic information about the patients. BPRS 
primarily assesses the severity of psychotic symptoms, with total scores ranging 
from 18 to 126, where higher scores reflect more severe symptoms. PANSS is used 
to evaluate the presence and severity of various symptoms. CGI scale is applied 
to assess the patient’s overall condition and therapeutic efficacy. SDSS measures 
the extent of social functional deficits. SQLS is designed to evaluate the 
quality of life in schizophrenia. For detailed information, please see Table 2.

**Table 2. S3.T2:** **Schedule of enrollment, interventions, assessments, and visits 
of patients**.

	Recruitment	Baseline	Assessments		
			Weekend 2	Weekend 4	6-month follow-up
Time point		T0	T1	T2	T3
Prescreening for eligibility, consenting and clinical interview					
Recruitment					
Eligibility screening	√				
Informed consent	√				
Allocation	√				
Primary outcome assessment					
MCCB		√	√	√	√
Second outcome assessment					
BPRS		√	√	√	√
PANSS		√	√	√	√
CGI		√	√	√	√
SDSS		√	√	√	√
SQLS		√	√	√	√
GIQ		√			
MRI		√	√	√	√
Blood sample collection (BDNF and GDNF levels)		√		√	√
Safety					
ARS			√	√	

A checkmark (√) indicates the time point at which each assessment is 
carried out. MRI, magnetic resonance imaging.

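### The HD-tDCS adverse reaction scale is scheduled only at T1 and T2, which does not match its prompt-identification role, and no collection point common to all four groups is stated for other adverse events

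*Protocol article*

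**What the plan says.** Section 2.13 (Harms) describes one purpose-built safety instrument: an "assessment form specific to HD-tDCS was developed for this study, encompassing" "common adverse reactions such as headache, skin tingling, fatigue, itching", burning and local discomfort. It says that the design of the scale helps with "the prompt identification and management of any issues that may arise during the" process.

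Table 2 (section 2.9) has one row under Safety, the ARS, ticked at T1 and T2 and blank at T0 and T3. Its footnote says that a tick "indicates the time point at which each assessment is" made. The row is not limited to particular groups. The columns are headed weekend 2 for T1 and weekend 4 for T2. Section 2.1 instead defines the assessment points as "baseline (T0), after 10 sessions (T1), after 20 sessions (T2), and after six" months of follow-up. Section 2.6 sets the exposure: "HD-tDCS will be conducted 5 times per week, over a 4-week period, 20" sessions.

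Section 2.13 also provides a second route. All adverse events are to be "systematically recorded in the CRF with respect to their incidence, types, and" severity, and a summary for Groups 1 to 4 is meant to "enable safety comparisons across the different interventions". Under section 2.1, Group 4 continues medication and standard care with no HD-tDCS or CCRT sessions.

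**The concern.** The text gives the scale a job that its schedule serves poorly. Tingling, itching and burning are tied to individual stimulation sessions, but the form is completed once per block of 10. Headache and fatigue are on the form and are also complaints that patients can have before treatment. Without a baseline form, they cannot be classed as new or pre-existing in a given patient.

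The CRF route is broader, but the article does not say when, or by what question, events are elicited in each arm. Treated patients meet a therapist on up to 20 occasions and controls on none, so unscheduled reports may reach the CRF more readily from Groups 1 to 3. A difference between arms in the percentage affected would then mix harm with opportunity to report. This matters the more because section 2.12 reports that a data monitoring committee was waived, so the harms evidence rests on these forms and the CRF.

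**Working it through.** The plan states no figure for adverse-event ascertainment, so there is none to reproduce. The check sets the schedule beside the text and counts.

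1. **Forms per session.** Sessions: 5 per week × 4 weeks = 20 (section 2.6). ARS occasions: 2 (Table 2). 20 / 2 = 10 sessions per form. At 5 sessions per week, 10 / 5 = 2 weeks between forms. A reaction early in a block could wait about two weeks before this form records it.

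2. **Baseline.** There is no ARS tick at T0. For headache and fatigue, a positive entry at T1 may be new, worsened or unchanged since before treatment, and the form does not separate these. With 12 per group (section 2.11), one patient with a pre-existing complaint changes that group's percentage by 1 / 12 = 8.3 points.

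3. **Opportunity to report.** Every group has four assessment points, T0 to T3. Groups 1 to 3 add up to 20 treatment contacts and Group 4 adds 0. The counts are up to 24 against 4. Routine clinical contacts are not described by group and are left out. The only scheduled safety form shared by all arms is the one built for HD-tDCS.

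4. **Meaning of T1 and T2.** Section 2.1 counts sessions, while Table 2 uses weekends 2 and 4. Group 4 has no sessions, so only the calendar reading can apply to it. For a patient who stops therapy before session 10, the calendar reading gives a T1 form and the session reading does not. The article does not say which governs.

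5. **Can the under-count be sized?** Only under assumptions. Suppose a reaction occurs in 5% or 10% of sessions, independently, and each form captures only the latest session.
   - At 5%: true incidence over 20 sessions is 1 − 0.95^20 = 64.2%. Two forms would show 1 − 0.95^2 = 9.8%. The gap is 54.4 points.
   - At 10%: 1 − 0.90^20 = 87.8% against 1 − 0.90^2 = 19.0%. The gap is 68.8 points.
   - With perfect two-week recall, the gap is 0 in both cases.

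   The document gives neither a per-session rate nor a recall window. The range of 0 to about 69 points illustrates the uncertainty and is not an estimate.

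**The case against.** The strongest reply is that the four-group comparison does not depend on the ARS. In section 2.13 it follows the sentence on recording all adverse events in the CRF, and section 2.14 adds weekly CRF review by the principal investigator through therapy and follow-up. That is correct. A reader might infer that the scale cannot support any comparison between arms, and the document does not bear this out: the ARS row covers all groups, and headache and fatigue can be reported in any of them. Weekly review, however, checks what has been entered and does not ask patients anything.

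Two other inferences also fail.
- A reader might conclude that patients who stop because of harm are lost. Table 2 labels T1 and T2 by week, analysis is by intention to treat, and a serious reaction leads to health evaluation, ethics-committee notification and CRF recording.
- A reader might conclude that psychiatric worsening goes unseen. BPRS, PANSS and CGI are scheduled at T0, T1, T2 and T3 without restriction by group.

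On baseline complaints, randomisation balances them in expectation, so the missing T0 form does not by itself bias the comparison between groups. It does leave each patient's events unattributable and the stated percentages inflated by existing complaints, and with 12 per group chance imbalance remains possible.

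Finally, a condensed article may leave per-session check sheets and the wording of adverse-event questions to the full protocol. That limits the criticism of the CRF route. It does not excuse the ARS schedule, which the article itself fixes in Table 2 and which sits poorly with the role given to the scale.

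**Conclusion.** The point holds as a modest, inexpensive improvement. One form per 10 sessions with no baseline does not match the prompt-identification role in section 2.13, and it prevents new headache or fatigue from being separated from pre-existing complaints within a patient. The comparison across Groups 1 to 4 draws also on CRF adverse events, for which no common collection point is stated, and treatment contacts differ (up to 20 against none), so unscheduled reports may be collected unequally. The direction and size of any net error cannot be derived from the document: missed transient reactions would lower the counts, and pre-existing complaints would raise them. The conclusion rests on reading Table 2 as the complete ARS schedule, as its footnote indicates. The CRF part also assumes that no common elicitation is specified in a fuller document that is not shown.

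**What to change.** Reconcile section 2.13 with Table 2 as follows.
- Add the ARS at T0 in all four groups, and a brief ARS after each session in Groups 1 to 3.
- State that T1 and T2 are the week-2 and week-4 visits for every participant, including those who stop therapy early.
- Ask one identical, open adverse-event question in all four groups at T0, T1 and T2.
- Base the cross-group comparison on these common visits, counting events that are new or worsened since T0. Report the per-session data descriptively.

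This takes an amended row in Table 2, one timing definition and one question, and uses visits and therapists already in place. The cost is a few minutes per session and probably a higher reported reaction rate. Per-session forms should be kept from the blinded assessors. The change does not remove reporting differences that arise because there is no sham control, a limitation that the Discussion already acknowledges. It concerns data collection only and alters no treatment rule.

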### 2.11 Statistical Analysis Plan

The sample size was calculated using G*Power software (version 3.1.9.7, 
Heinrich-Heine-Universität Düsseldorf, Düsseldorf, Germany), 
employing an F-test and a repeated-measures ANOVA model. In this study, we 
established the probability of a Type I error (α) at 0.05, the 
probability of a Type II error (β) at 0.20, and the statistical power (1 
- β) at 0.80, with an effect size (f) of 0.25. The required sample size 
was calculated to be 36 participants. Accounting for a 20% dropout rate and 
ensuring equal group sizes, the target sample size was determined to be 48 
participants, with 12 participants per group. The calculation of the sample size 
mentioned above is based on the sample size calculation methods adopted in 
previous literature [50]. An article suggests that when designing a preliminary 
study with no prior information for reference, a sample size of 12 participants 
per group is appropriate based on feasibility, improvements in the precision of 
mean and variance estimates, and regulatory considerations [51]. The 
sample size in this study satisfies the previously mentioned criteria and will 
offer enough statistical power to achieve the objectives.

We will utilize histograms and the Shapiro-Wilk test to assess the normality of 
the data distribution. For normal distribution data, continuous variables will be 
reported as mean ± standard deviation, whereas categorical data will be 
presented as frequencies (n) and percentages (%). Statistical tests such as 
one-way analysis of variance (ANOVA), Mann-Whitney U test, *t*-test, and chi-square 
test will be employed to assess baseline differences among groups. In accordance 
with the Consolidated Standards of Reporting Trials (CONSORT) guidelines, all 
analyses will be conducted using the intention-to-treat (ITT) principle, whereby 
participants will be analyzed according to their original randomization group. To 
address missing data within the ITT framework, we will employ linear 
mixed-effects models. These models are appropriate for making valid inferences 
under the missing-at-random assumption and are well-suited for managing the 
unbalanced data resulting from participant drop-out. To specifically assess the 
synergistic effect between HD-tDCS and CCRT, the models will incorporate the 
HD-tDCS × CCRT interaction as a fixed effect. We will conduct 
sensitivity analyses by comparing the results derived from mixed-effects models 

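### Section 2.13 rests its HD-tDCS safety comparison on four arms of 12, which is imprecise; the sharper 24 v 24 contrast is not specified, and the blanket ITT rule suits safety poorly

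*Protocol article*

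**What the plan says.** Section 2.13 (Harms) gives the examination of HD-tDCS safety as its purpose. It describes a reaction form built for HD-tDCS, which covers headache, fatigue and several local skin sensations. The final report is to summarise adverse events for each of Groups 1 to 4, by how often they occur, how severe they are and what share of patients is affected. The section then says this will "enable safety comparisons across the different interventions". It names no test, no power and no pooled comparison.

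Section 2.11 sets a target of 48 "participants, with 12 participants per group". It also says that all "analyses will be conducted using the intention-to-treat (ITT) principle, whereby" patients are analysed in the group to which they were randomised. Section 2.13 makes no exception for safety.

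Section 2.1 gives HD-tDCS to Groups 1 and 2. Group 3 receives CCRT only, and Group 4 continues usual care without "undergoing any HD-tDCS or CCRT sessions". Table 2 schedules the adverse reaction scale at T1 and T2, with no restriction by group.

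**The concern.** The safety question is about one factor, HD-tDCS, but the summary is laid out by four cells of 12. At that size a table with no visible difference says little, and a reader could take it as reassurance. The design can put all 24 patients allocated to HD-tDCS against the 24 who are not. Section 2.11 uses this factorial structure in the outcome models, through the HD-tDCS × CCRT term, but section 2.13 does not mention it.

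The as-randomised rule adds a smaller problem. A patient allocated to Group 1 or 2 who never has a stimulation session would stay in the HD-tDCS denominator. If reactions are more frequent under current than without it, this pulls the reported rate down, in the reassuring direction. Section 2.12 waives the data monitoring committee, so the end-of-study table is the only between-group safety comparison that the article describes.

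**Working it through.** **Inputs from the protocol.** There are 12 patients per group in four groups. HD-tDCS is given in two of them, so 2 × 12 = 24 with and 24 without. Section 2.11 "established the probability of a Type I error (α) at 0.05"; sidedness is not stated, so two-sided is assumed here.

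**Inputs assumed.** The protocol gives no adverse-event rates, so ranges are shown.

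**The plan's own figure.** There is none for safety. The efficacy size can be reproduced. The method is described as "employing an F-test and a repeated-measures ANOVA model", with power (1 − "β) at 0.80, with an effect size (f) of 0.25". Taking the group-by-time interaction with 4 groups, 4 measurements, an assumed correlation of 0.5 and sphericity, the noncentrality is f²·N·m/(1 − ρ) = 0.0625 × 36 × 4/0.5 = 18. This gives power 0.825 at N = 36. Then 36/0.80 = 45, and rounding up to four equal groups gives 48. The arm size of 12 therefore comes from efficacy alone.

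**Zero events.** The exact two-sided 95% upper limit is 1 − 0.025^(1/n).
- n = 12: 1 − 0.025^(1/12) = 0.265
- n = 24: 1 − 0.025^(1/24) = 0.142

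**Smallest significant split.** For x v 0 events with n per side, the two-sided Fisher p-value is 2·C(n,x)/C(2n,x).
- 12 v 12, 4 v 0: 2 × 495/10,626 = 0.093
- 12 v 12, 5 v 0: 2 × 792/42,504 = 0.037
- With 1 or 2 events in the comparator, 7 v 1 (p = 0.027) or 8 v 2 (p = 0.036) is needed.
- 24 v 24, 5 v 0: 2 × 42,504/1,712,304 = 0.0496

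The count needed against zero is 5 in both cases, but 5/12 is 42% and 5/24 is 21%.

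**Power.** This is the sum of Bin(x; n, p₁)·Bin(y; n, p₂) over all (x, y) for which Fisher gives p < 0.05.

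| Assumed rates | 12 v 12 | 24 v 24 |
|---|---|---|
| 30% v 10% | 0.095 | 0.31 |
| 40% v 10% | 0.23 | 0.60 |
| 50% v 10% | 0.43 | 0.83 |

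For comparator rates from 0% to 30%, 80% power needs a difference of about 50 to 60 percentage points at 12 v 12, and about 27 to 43 points at 24 v 24.

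**As-randomised denominators.** Suppose k of 12 patients are never stimulated and report no event, and the rate among the stimulated is r. The reported rate is then r × (12 − k)/12. For r = 50%, it is 50% with k = 0, 46% with k = 1 and 42% with k = 2. The protocol gives neither k nor r, so only the direction follows from the text. The 20% in section 2.11 is dropout, which is not the same as never starting.

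**The case against.** The strongest reply is that section 2.13 promises description and nothing more. Showing every arm side by side does let readers compare them, and no test or power is claimed. That stands. A reader might infer that the protocol asserts an inferential property that it lacks, but the text does not go so far. The fault is an optimistic sentence, not a wrong figure.

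A reader might also infer that the 24 v 24 contrast has been rejected. The article is merely silent. The counts of patients affected can be added up from the four-group table, and a fuller protocol or SAP might specify the contrast.

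It is tempting to say that a large HD-tDCS excess would usually be missed. For tingling, itching and burning this is unproven. Groups 3 and 4 receive neither current nor sham, so their rates may be near zero, and a large difference would show even at 12 v 12.

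On ITT, the surrounding sentences in section 2.11 concern missing outcome data and mixed models, so the rule may never have been meant for harms. That is a fair reading of the context, but the wording covers all analyses and section 2.13 does not limit it.

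Finally, pooling is not a cure, and it could hide harm specific to the combination. Both points stand. They are reasons to keep the four-group table beside the pooled contrast.

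**Conclusion.** The point holds as a minor one. At 12 per arm the promised safety comparison is imprecise: an upper limit of 26% after zero events, and at least 5 v 0 for significance. This matters mainly for less common or non-specific events. The 24 v 24 contrast fits the stated aim better and costs no patients: the upper limit falls to 14%, and power for 40% v 10% rises from 0.23 to 0.60. It remains limited, at 0.31 for 30% v 10%. The power figures rest on assumed event rates and a two-sided Fisher test; the zero-event limits need neither.

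The literal ITT rule suits safety poorly because it counts unexposed patients as exposed. The bias is downwards if stimulation raises event rates, and the documents do not let one say by how much. They do not support calling the safety statement false, or saying that the pooled contrast was ruled out.

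**What to change.** In section 2.13:
- Keep the four-group table and label it descriptive.
- Add HD-tDCS (Groups 1+2) v no HD-tDCS (Groups 3+4), with a risk difference and an exact 95% confidence interval. Use the adverse reaction scale already scheduled at T1 and T2, asked in the same way in all groups.
- Replace the sentence on enabling comparisons with a statement that an absence of observed difference is not evidence of equal safety.

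In section 2.11, exempt safety from the ITT rule and classify patients by therapy received, defined as at least one session.

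The cost is a few sentences, with no new data and no more patients. Pooling assumes that CCRT does not alter reactions to HD-tDCS, and it could mask harm specific to the combination; the retained four-group table lets readers check this. Classifying by therapy received also means that the safety contrast is no longer strictly as randomised if some patients never start, so their number should be reported.
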